3. CDISC

CHILD:

1. Conners' Continuous Performance Test (CPT-II)

The blinded clinicians, parents and children will complete their assessments at weeks 1, 8, 16 (control), 20 (intervention), 24 (intervention), 28 (control) and 32 (control). The children and their parents will come down to the clinic for these scheduled assessments. The blinded clinician will contact the child's school teacher(s) and obtain feedback about the child's behavior in school. This will be made known to parents during the briefing session held prior to enrolment.

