## 5. Study Design

Our hypothesis is that children with ADHD receiving treatment with the BCI-based training will improve to a greater extent than the control group. This will be organized as a prospective single blind randomized clinical trial (clinicians blinded to subjects treatment arm), with the comparator arm being a

wait-list control. All subjects will eventually receive the BCI intervention but subjects in the control arm will not receive it until week 9.

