### **5.1 Intervention Group**

86 subjects in the intervention group will take part in a total of 24 sessions spread over an 8-week period, followed by one-monthly booster sessions for another 3 months and a final follow-up review 1 month after the completion of the training session. If sessions are missed during the 8-weeks period due to unforeseen circumstances (e.g. sickness, travel plans), arrangements will be made for participants to attend up to 5 BCI-based therapy sessions per week. All participants will have to complete a minimum of 20 sessions within the 8-weeks period for treatment efficacy.

Each subject will first need to master a simple concentration task before moving on to play a series of training tasks. Each task employs the BCI system, and is controlled by the child's concentration. As the child attends to activities on a computer screen, their EEG waves will be recorded simultaneously via the EEG sensors through Bluetooth technology.

In addition, as part of the treatment protocol, they will be tasked to do a set of MCQ on the computer. The task will consist of both Math and English questions and will be matched to their grade level. During the second session, subjects will be administered MCQs at their appropriate grade level.

Administering of MCQs will be done at alternate intervention sessions over the 8-week period and during each of the 3 monthly 'booster' sessions. Their EEG activity will be recorded during these tasks as well. Subjects will be advised to concentrate during the task just as they did during the BCI intervention. This will train the child to generalize their 'concentration skills' learnt during the BCI training to their academic tasks.

The children in this group will be followed up by their child psychiatrist at the following weeks: Week 1, 8, and 20. At the end of this study phase, the clinician will discuss with the parents about their child's condition and a progress report will be provided. If parents are keen, they will be referred to CGC or REACH for further follow up and treatment.

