### **5.2 Control Group**

86 subjects in the control group will not receive BCI training during the first 8 weeks of their study participation; they will act as controls. At week 9, subjects in this group will go through the BCI training similar to the intervention group. If sessions are missed during the 8-weeks period due to unforeseen circumstances (e.g. sickness, travel plans), arrangements will be made for participants to attend up to 5 BCI-based therapy sessions per week. All participants will have to complete a minimum of 20 sessions within the 8-weeks period for treatment efficacy.

They will take part in a total of 24 sessions spread over an 8-week period, followed by one-monthly booster sessions for another 3 months. Subjects will be tasked to do a set of MCQs on the computer. The task will consist of both Math and English questions and will be matched to their grade level. The procedure for MCQ administration will be exactly the same as the intervention group. Administering of MCQs will be done at the end of alternate intervention sessions over the 8-week period and during each

of the 3 monthly 'booster' sessions. Their EEG activity will be recorded during these tasks as well. Their participation in the research study will last 8 months. The subjects in the control group will complete the exact same questionnaires at the same time-points as the intervention group.

All children in this group will be followed up by their child psychiatrist at the following weeks: Week 1, 8, 16, 28 and 32.

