#### **6.5 Blinding**

Clinicians conducting the study assessments will be blinded to the study arm. Teachers who will be providing feedback to the clinicians will be blinded as well. Study Investigators, study personnel (including the SCRI study team), parents and subjects are not blinded in this study. Parents and subjects will be advised regularly not to inform the clinicians or teachers to which group the subjects are assigned.

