| Clinical Global Impression - Improvement Scale                            | Group 1     |                     | XX       | XX           |              | X       |             | X         |         |
|                                                                           | Group 2     |                     |          |              | X            |         | X           |           | X       |
| ADHD Rating Scale                                                         | Group 1     |                     | XX       | XX           |              | X       |             | X         |         |
|                                                                           | Group 2     |                     |          |              | X            |         | X           |           | X       |
| Pediatric Adverse Event Rating Scale (PAERS)                              | Group 1     |                     |          | X            |              | X       |             | X         |         |
|                                                                           | Group 2     |                     |          |              | X            |         | X           |           | X       |

NB: All assessment visits will be completed accordingly to the assessment week within the window period of +/- 5 working days.

Figure 1: Study Visit and Procedure for Both Groups

**Appendix A****Schedule 1: Gantt schedule of Phase 2 overall study design and timelines for intervention & control groups.**[figure not shown]**Assessments for both intervention and control group**

| Week 0                      | Week 1
(+/- 5 work days)   | Week 8
(+/- 5 work days)                              | Week 16
(+/- 5 work days)  | Week 20 (Intervention)
Week 28 (Control)
(+/- 5 work days) | Week 24 (Intervention)
Week 32 (Control)
(+/- 5 work days) |
|------------------------------------|---------------------------------------------|------------------------------------------------------------------------|---------------------------------------------|-----------------------------------------------------------------------------------------------------|-----------------------------------------------------------------------------------------------------|

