#### **11.2.3 Analysis of primary and secondary endpoints**

Change in the inattentive score on the ADHD Rating Scale as rated by clinicians at week 8 will be compared between the intervention group (post-BCI) and control groups (pre-BCI) using the two sample t test. Mean difference of the changes between the two groups and its associated 95% confidence interval will be reported. Comparison of change scores for the continuous secondary outcomes at week 8 between the two groups will also be conducted by using the two sample t test or Mann-Whitney U test, where appropriate. Chi squared test or Fisher's exact test, where appropriate, will be used for categorical secondary outcomes.

Booster effect will be analyzed by first pooling paired data before and after the boosters in the two groups. Change in efficacy endpoints as rated by clinicians and parents at week 20 from week 1 in the intervention arm and changes at week 28 from week 9 in the waitlist control group. These pooled changes before and after the boosters will be summarized; and comparisons of efficacy endpoints pre and post boosters will be made in the pooled data by using the paired t test or Wilcoxon signed rank test, where appropriate. The above will also be conducted at week 24 from week 1 in the intervention arm and week 32 from week 9 in the waitlist control to assess the effect the sustainability of the effect of the BCI system.

The longitudinal ADHD ratings, and other clinician's scales will be explored by the generalized estimating equations approach, both assessing the time trend and the difference in time trend between groups.

Frequency and percentage of the adverse events highlighted in the side effect checklist will be summarized for the pooled sample since the BCI program is administered to all subjects for all those that receive at least one BCI session.

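### Clinician blinding is claimed with no time limit, but every assessment week after week 8 belongs to one arm only; the clinician forms at week 8 also need reconciling

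*Protocol*

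**What the plan says.** **Blinding.** Section 5 calls the study a "prospective single blind randomized clinical trial (clinicians blinded to subjects treatment arm"). Section 6.5 states: "Clinicians conducting the study assessments will be blinded to the study arm". Section 4 applies the same label to the whole visit list: "The blinded clinicians, parents and children will complete their assessments at weeks 1, 8, 16 (control), 20 (intervention), 24 (intervention), 28 (control"), followed by week 32 for controls. None of the three limits the claim to particular weeks. Parents and children are not blinded. The only masking measure described is advice to families, in Section 6.5, not to tell clinicians or teachers the arm.

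**Schedule.** Section 4, Table 1 and the assessment table in Section 6.6 place weeks 1 and 8 in both arms, weeks 16, 28 and 32 in the control arm, and weeks 20 and 24 in the intervention arm. Visits take place "within the window period of +/- 5 working days". Section 5.2 nevertheless says: "The subjects in the control group will complete the exact same questionnaires at the same time-points as the intervention group".

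**Use of the later ratings.** Section 11.2.3 plans to explore the longitudinal ADHD ratings and the other clinician scales by GEE, "both assessing the time trend and the difference in time trend between groups".

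**Clinician forms at week 8.** Section 4 lists the PAERS among the clinician's forms from week 8 onwards and names no arm. In Table 1 the row "Pediatric Adverse Event Rating Scale (PAERS") has a week 8 mark on the Group 1 (intervention) line only.

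**The concern.** The comparator is a wait-list, and families know their arm. The clinician's rating is therefore the main protection against expectancy bias, and it carries the primary endpoint. If the visit week tells the rater the arm, later clinician ratings would be reported as blinded when the schedule does not support that. The between-group trend analysis would inherit the same description.

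The form set raises a separate question at week 8. If the clinician who scores the ADHD Rating Scale has an extra form for intervention children only, the arm could be disclosed at the visit that supplies the primary endpoint.

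**Working it through.** The plan attaches no figure to this point and the sample size plays no part in it. The check compares visit weeks by arm, then compares the passages on the week 8 forms.

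**1. Visit weeks by arm** (Section 4, Table 1)

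| Arm | Assessment weeks |
|---|---|
| Intervention | 1, 8, 20, 24 |
| Control | 1, 8, 16, 28, 32 |
| Shared | 1, 8 |
| One arm only | 16, 20, 24, 28, 32 |

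All five weeks after week 8 are arm-specific.

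**2. Could the visit windows blur this?** Five working days is about one calendar week, so each window runs from one week before to one week after the nominal week: 15–17 (control), 19–21 (intervention), 23–25 (intervention), 27–29 (control) and 31–33 (control). The gap between two windows is the difference in nominal weeks minus 2.

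| Intervention week | Control week 16 | Control week 28 | Control week 32 |
|---|---|---|---|
| 20 | 20 − 16 − 2 = 2 | 28 − 20 − 2 = 6 | 32 − 20 − 2 = 10 |
| 24 | 24 − 16 − 2 = 6 | 28 − 24 − 2 = 2 | 32 − 24 − 2 = 6 |

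The smallest gap is 2 weeks, so no windows overlap across arms.

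**3. Does another passage restore a common calendar?** The Section 5.2 sentence on shared time-points would, but its own next paragraph lists weeks 1, 8, 16, 28 and 32 for controls. Section 5.1 has "The children in this group will be followed up by their child psychiatrist at the following weeks: Week 1, 8, and 20", which is a different calendar and also omits the week 24 visit that Section 4 and Table 1 schedule. Section 2.2.2, item 6, names week 28 for the intervention group, but items 2 and 4 and the schedule give week 24. Even if item 6 were taken literally, weeks 16, 20, 24 and 32 would remain arm-specific. No dummy visits, and no raters kept unaware of the visit week, are described.

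**4. Which analyses use the later ratings?**
- The primary endpoint (Sections 2.1.2 and 11.2.3) compares change from week 1 to week 8. Both visits are shared.
- The booster and sustainability analyses (Section 11.2.3) are pooled, paired, within-subject changes.
- The GEE is the one planned between-arm use of clinician ratings made after week 8.

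**5. Forms at week 8.** In Table 1, the efficacy entries that both groups have at weeks 1 and 8 are marked XX, and arm-specific later entries are marked X on that group's line. PAERS at week 8 has a single X on the Group 1 line, which fits a form for Group 1 only. Section 4 gives no such limit, and Section 5.2 says controls complete the same questionnaires. The passages do not agree.

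**The case against.** **The primary endpoint is safe from the calendar.** A reader might infer that the arm-specific schedule unblinds the main result. It does not, because both arms attend weeks 1 and 8. The other between-arm comparisons at week 8 are equally unaffected. This stands in full.

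**Knowing the arm matters less after week 8.** Controls start the training at week 9, so at every later visit a child in either arm is due to have had it. The arm no longer separates treated from untreated children, which is the distinction that blinding chiefly protects in a wait-list design. Section 11.2.3 already presents the GEE as exploratory. Both points stand and keep the consequence small. They do not make the unlimited blinding statements correct.

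**Disclosure is inferred.** A reader might conclude that every later rating is in fact unblinded. That requires the rater to know the study week, which the protocol does not say. It is likely, since visits are labelled by week and psychiatrist follow-up runs on arm-specific calendars, but what the text supports is that blinding cannot be maintained as described.

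**The PAERS mark may not mean what it seems to.** A reader might infer that the form certainly reveals the arm at week 8. Some Table 1 marks sit on one group's line although they apply more widely: C-DISC appears on the Group 1 line and KBIT-2 on the Group 2 line. Those are XX marks, however, so the single X still favours a Group 1 reading. Disclosure would also require that the efficacy rater completes the form, and before or together with the rating. The protocol fixes neither. The point remains conditional.

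**The Section 5.2 sentence is loose wording.** The paragraph after it lists the control weeks, so a site is unlikely to be misled. It still contradicts the schedule on a matter that bears on blinding.

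**Conclusion.** The concern holds in a limited form. The protocol claims clinician blinding with no time limit, but all five scheduled weeks after week 8 belong to one arm, with at least about 2 weeks between windows of different arms and no masking of visit week. Blinding to arm therefore cannot be maintained as described after week 8. This assumes that raters know, or can work out, the study week.

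The consequence falls on the description of the later clinician ratings and on the exploratory between-group trend. The documents do not support a claim that the visit calendar compromises the primary endpoint, and they give no basis for estimating the size of any bias in the later ratings.

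The week 8 form set is the only route to the primary rating. It matters only if Table 1 is followed as marked and the efficacy rater completes the PAERS. It is worth settling because the primary rating depends on the blind at that visit. The changes should be made, but none of them calls the main comparison into question.

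**What to change.** 1. Reconcile Section 4, Section 5.2 and the PAERS row of Table 1 so that clinicians have the identical form set in both arms at week 8. Section 9.2.1 already collects adverse events from consent onwards, so a control form at week 8 fits the plan. Because Section 11.2.3 summarises adverse events in children with at least one training session, state that control PAERS data at week 8 precede exposure.
2. In Sections 4, 5 and 6.5, limit the statement of clinician blinding to weeks 1 and 8.
3. In Section 11.2.3, state that clinician ratings after week 8, and the GEE between-group trend that uses them, are not reliably blinded.
4. Correct the time-points sentence in Section 5.2 to match the schedule. If it was meant as time since the start of training, say so.

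The cost is one extra form for controls at week 8, some wording changes and a slightly less favourable blinding claim. The sample size, endpoints and visits stay as they are.

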## 5. Study Design

Our hypothesis is that children with ADHD receiving treatment with the BCI-based training will improve to a greater extent than the control group. This will be organized as a prospective single blind randomized clinical trial (clinicians blinded to subjects treatment arm), with the comparator arm being a

wait-list control. All subjects will eventually receive the BCI intervention but subjects in the control arm will not receive it until week 9.

### **5.1 Intervention Group**

86 subjects in the intervention group will take part in a total of 24 sessions spread over an 8-week period, followed by one-monthly booster sessions for another 3 months and a final follow-up review 1 month after the completion of the training session. If sessions are missed during the 8-weeks period due to unforeseen circumstances (e.g. sickness, travel plans), arrangements will be made for participants to attend up to 5 BCI-based therapy sessions per week. All participants will have to complete a minimum of 20 sessions within the 8-weeks period for treatment efficacy.

Each subject will first need to master a simple concentration task before moving on to play a series of training tasks. Each task employs the BCI system, and is controlled by the child's concentration. As the child attends to activities on a computer screen, their EEG waves will be recorded simultaneously via the EEG sensors through Bluetooth technology.

In addition, as part of the treatment protocol, they will be tasked to do a set of MCQ on the computer. The task will consist of both Math and English questions and will be matched to their grade level. During the second session, subjects will be administered MCQs at their appropriate grade level.

Administering of MCQs will be done at alternate intervention sessions over the 8-week period and during each of the 3 monthly 'booster' sessions. Their EEG activity will be recorded during these tasks as well. Subjects will be advised to concentrate during the task just as they did during the BCI intervention. This will train the child to generalize their 'concentration skills' learnt during the BCI training to their academic tasks.

The children in this group will be followed up by their child psychiatrist at the following weeks: Week 1, 8, and 20. At the end of this study phase, the clinician will discuss with the parents about their child's condition and a progress report will be provided. If parents are keen, they will be referred to CGC or REACH for further follow up and treatment.

### **5.2 Control Group**

86 subjects in the control group will not receive BCI training during the first 8 weeks of their study participation; they will act as controls. At week 9, subjects in this group will go through the BCI training similar to the intervention group. If sessions are missed during the 8-weeks period due to unforeseen circumstances (e.g. sickness, travel plans), arrangements will be made for participants to attend up to 5 BCI-based therapy sessions per week. All participants will have to complete a minimum of 20 sessions within the 8-weeks period for treatment efficacy.

They will take part in a total of 24 sessions spread over an 8-week period, followed by one-monthly booster sessions for another 3 months. Subjects will be tasked to do a set of MCQs on the computer. The task will consist of both Math and English questions and will be matched to their grade level. The procedure for MCQ administration will be exactly the same as the intervention group. Administering of MCQs will be done at the end of alternate intervention sessions over the 8-week period and during each

of the 3 monthly 'booster' sessions. Their EEG activity will be recorded during these tasks as well. Their participation in the research study will last 8 months. The subjects in the control group will complete the exact same questionnaires at the same time-points as the intervention group.

All children in this group will be followed up by their child psychiatrist at the following weeks: Week 1, 8, 16, 28 and 32.

## **6. Methods and Assessments**

### **6.1 Selection of Subjects**

This study will enroll 172 children aged between 6 to 12 years with ADHD from CGC.

### **6.2 Enrolment from Clinic**

First contact with the subjects will be as follows:

The treating doctor will inform parents of potential subjects. An information letter will be provided to the parents of potential subjects to invite them to learn more about the study. After parents have indicated interest in knowing more about the BCI study, the protocol administrator will contact parents of potential subjects to arrange a clinic visit for a briefing session where the study will be explained to them in greater detail..

Potential subjects who are not enrolled with the clinic will be advised to register as a clinic patient first before recruitment into the study.

### **6.3 Briefing session for all potential subjects**

During briefing sessions, the research team will provide an overview of ADHD and a demonstration of the BCI study will be conducted for parents to view. It will be highlighted that medication and psychosocial treatment represent current evidence-based treatment for this disorder. The BCI study will be presented as an alternative form of treatment that is being investigated in this study and parents will have ample time and opportunity to choose the treatment of preference. At the end of each briefing, parents will be provided with participant information sheets to take home for further consideration of participation.

After the briefings, parents will be contacted within one to two weeks to give all subjects sufficient time to contemplate and ask any queries pertaining to the study. If the parents indicate interest, a session will then be arranged for informed consent to be taken. Informed consent will be obtained from the parents, and assent from the subjects, prior to any form of assessment or intervention as part of the study. The blinded clinician will contact the child's school teacher(s) and obtain feedback about the child's behavior in school at various time points. This will be made known to parents during the briefing session. All trial-related procedures will only take place after informed consent has been obtained. A baseline assessment will be done to determine the child's eligibility for the study.

In the event that the child is eligible but the parents/legal guardians choose not to participate in the study, the parents/legal guardians will be offered an option to have the child be followed-up at the CGC.

Participation is strictly voluntary and at any point if the subject wishes to drop-out, he/she will not be restricted or punished for it.

